### Data analysis

Pain profiling will be undertaken irrespective of condition. Multivariate modelling (principal component analysis, cluster analysis or latent class analysis) to identify distinct pain patterns.Between-group comparisons (eg, independent T-tests, Mann-Whitney U) will explore between pain profile comparisons.Associations between pain profiles and clinical outcomes (eg, pain intensity, pain-related worrying, disability, quality of life) will be examined.Sensitivity analysis will be conducted between diagnostic groups and between matched samples.We believe that QST will identify somatosensory pain profiles, while CAP will identify psychological hypervigilance pain profiles, each associated with augmented central pain processing. Using the pain profiles combined with pain at 12 weeks, we will identify any relationship between potential augmented central pain processing and pain prognosis at 12 weeks (eg, persistent/worsening pain, pain>patient acceptable symptom state), informed by patterns of pain over 12 weeks and knowledge.Pain prognosis: Bivariable correlations will identify and permit comparison between baseline factors significantly associated with 3-month pain prognosis. Separate multivariable models will determine whether the CAP questionnaire, clinical QST or laboratory QST can increase prognostic precision beyond other clinical and demographic variables significantly associated with pain prognosis. Multivariable modelling will define whether and which combination of the CAP questionnaire and QST importantly improves prognostic determination. The proportion of the prognosis explained by each and by both the CAP questionnaire and clinical or laboratory QST will be determined.The reliability and validity of the stratification tool (combined CAP and clinical QST) will be tested across the study population, with sensitivity analysis conducted across the diagnostic groups, age, sex, social and ethnic strata.Test–retest reliability will be assessed using intraclass correlation between repeated CAP questionnaires and between two raters for simplified clinical QST.RMT, Cronbach’s alpha and confirmatory factor analysis will evaluate internal validity, consistency and factor structure. If multiple constructs with significant residual values exist, this will be further explored using principal component analysis of residuals, the eigenvalue criterion, residual correlations and theoretical understanding.Correlation analysis will assess external validity against self-reported questionnaires and laboratory QST.Mechanistic underpinning: The dataset will be randomly divided into development and validation sets. Exploratory and confirmatory factor analyses will determine whether there are subgroups of the population for whom the stratification tools function differently. Correlations between CAP scores and clinical and laboratory QST indices of augmented central pain processing will be identified. Bivariate and multivariable models will ascertain whether associations may be explained by one or more characteristics linked to maladaptive pain processing (sleep disturbance, fatigue, anxiety, depression, cognitive impact, catastrophising).Relevance to patient-centred outcomes: Bivariate associations between CAP or QST and patient-reported outcome measures scores will be determined through linear regression. The proportion of participant-reported pain or other patient-reported outcome measures explained by CAP scores, clinical and/or laboratory QST measures, will be identified as R^2^ in multivariable regression.Qualitative data will be analysed using reflexive thematic analysis following the stages outlined by Braun and Clarke.^97^ A reflexive journal will be kept throughout the data collection process. Data will be coded inductively primarily, while also being informed by the Normalisation Process Theory^90 91^ commonly used to support evaluation in health interventions and inform the tool’s theoretical acceptability and feasibility. A ‘critical friend’^98^ will code a sample of transcripts independently until consensus is reached. After the consensus is reached, all remaining transcripts will be coded. NVivo V.15 will assist in managing, analysing, and visualising the qualitative data set. A thematic map may also visually represent the main themes developed.

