**Methods and analysis:**

This prospective observational study will recruit 250 individuals with inflammatory arthritis, osteoarthritis, chronic low back pain or fibromyalgia from existing cohorts, primary or secondary care. Participants will complete validated patient-reported outcomes at baseline, 6 and 12 weeks, with no additional intervention. The risk stratification tool completed at baseline will include clinical QST (Pressure Pain Threshold, Temporal Summation of Pain, Conditioned Pain Modulation), tender point count and the CAP questionnaire. Baseline laboratory versions of the clinical QST, plus Heat Pain Threshold, Offset Analgesia and the Central Sensitisation Inventory short form-9 questionnaire, will provide pain profiling to evaluate the predictive validity and psychometric properties of the tool. Data collection will include demographics, medical history, cognitive and neurological assessments and sleep quality via actigraphy (Actigraph wGT3X-BT). Interviews with patients and healthcare professionals will inform refinement, feasibility and acceptability of the tool.

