### Sample size

A sample size of 250 participants at baseline, with an anticipated 200 individuals completing the follow-up questionnaires, accounting for 20% attrition.^92^ Provides additional statistical power and robustness to detect differences, allowing for more precise estimates of interactions and better management of potential missing data, therefore enhancing the validity of our findings.

Rasch measurement theory (RMT) to determine the structural validity of the risk stratification tool assumes that item calibrations lie within ±½ logit of stable values within a 99% CI, resulting in an overall sample size between 108 and 243, from best to poor targeting.^93 94^ This aligns with the Consensus-based Standards for the selection of health Measurement Instruments recommendations RMT analysis.^95^

Pain profiles will be identified irrespective of condition, using multivariate models with 5 covariates, 95% power and an effect size of 0.5 would require 236 individuals to complete baseline assessments.^51^ For longitudinal modelling, assuming a correlation coefficient of 0.15 with 12-week pain, 164 participants with α=0.05 and 95% power.

Interviews will be conducted until theoretical saturation, the point at which additional data do not reveal any new themes that achieve conceptual depth.^96^ It is anticipated that 27 interviews will be conducted with participants and 22 HCPs and researchers (table 2).

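### Pain profiles are derived from the data and then compared by two-sample tests that do not exclude the variables forming them; on those variables the p-values are no evidence of distinct profiles, and the article is inconsistent about which variables those are

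*Protocol article*

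**What the plan says.** Under Data analysis, the pain-profiling block first forms the groups: "Multivariate modelling (principal component analysis, cluster analysis or latent class analysis) to identify distinct pain patterns". Next comes the comparison step: "Between-group comparisons (eg, independent T-tests, Mann-Whitney U) will explore between pain profile comparisons". The variables to be compared are not named. A separate sentence then deals with outcomes: "Associations between pain profiles and clinical outcomes (eg, pain intensity, pain-related worrying, disability, quality of life) will be examined". The same block states the expectation that "QST will identify somatosensory pain profiles, while CAP will identify psychological hypervigilance pain profiles", which implies that both QST and CAP are inputs.

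The Methods and analysis paragraph of the abstract describes the inputs differently. It says that the laboratory versions of the clinical QST, together with heat pain threshold, offset analgesia and CSI-9, "will provide pain profiling to evaluate the predictive validity and psychometric properties of the tool". CAP is not in that list. It appears there, and again under Experimental procedures, as part of the tool being evaluated.

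The Sample size section plans for "A sample size of 250 participants at baseline". It gives the profiling its own power statement: "using multivariate models with 5 covariates, 95% power and an effect size of 0.5 would require 236 individuals".

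**The concern.** A t-test or Mann-Whitney test between two groups assumes that membership was settled without looking at the variable tested. A clustering algorithm does the reverse: it chooses groups to be far apart on its inputs. A test on those inputs then rejects because the sample was partitioned, whether or not distinct profiles exist. A reader shown a table of profiles with small p-values against PPT, TSP, CPM or CAP would take it as support for distinct profiles, and it would be none.

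The input list matters for a second reason. If the profiles are to help evaluate the tool, as the abstract says, they need to be formed without the tool's components. If CAP helps to define them, their agreement with CAP is partly built in.

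**Working it through.** The article gives no error rate for these comparisons, so there is no figure to reproduce. The check asks how often the tests reject when no profiles exist.

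**Inputs.** N = 250 is from Sample size. Two-sided alpha 0.05 is assumed here; the article states 0.05 only for the longitudinal model. The clustering method (k-means, best of 5 starts), the number of profiles (2 or 3), normal data, the number of inputs and their correlation are all assumptions, because the article does not fix them.

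**One input, by hand.** Split a standard normal variable at its mean into two groups of 250/2 = 125.
- Group means are ±√(2/π) = ±0.798, so the difference is 1.596 SD.
- The within-group SD is √(1 − 2/π) = 0.603.
- t = 1.596 / (0.603 × √(1/125 + 1/125)) = 1.596 / 0.0763 ≈ 20.9.

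The critical value is about 1.97, so rejection is certain in practice although there is one population and no profile.

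**Several inputs, by simulation.** 300 runs per setting, one multivariate normal population, t-test between two of the clusters:

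| Inputs | Correlation | Rejection per forming variable, k = 2 / k = 3 | Independent outside variable, k = 2 / k = 3 |
|---|---|---|---|
| 1 | – | 100% / 100% | 3.7% / 5.0% |
| 4 | 0 | 86.5% / 84.5% | 4.3% / 5.0% |
| 4 | 0.3 | 100% / 90.9% | 3.0% / 4.3% |
| 5 | 0 | 85.4% / 82.4% | 5.3% / 4.0% |
| 5 | 0.3 | 100% / 93.4% | 4.0% / 7.0% |
| 9 | 0 | 75.7% / 72.5% | 6.7% / 3.7% |
| 9 | 0.3 | 100% / 98.9% | 4.7% / 5.3% |

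Mann-Whitney rates are within one percentage point of these. At least one forming variable was significant in every run of every setting, also after Bonferroni correction. The simulation standard error at 5% is √(0.05 × 0.95 / 300) = 1.3 points, so 3% to 7% for outside variables is consistent with the nominal level.

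**A second simulation** used six inputs (five QST measures plus CAP, an assumption), two clusters and 1,000 runs per setting. It gave 77%, 99.97% and 100% per forming variable at correlations 0, 0.2 and 0.4. An independent outside variable rejected in 4.3%, 3.9% and 6.0% of runs. The median largest difference between the two groups was 1.26, 1.15 and 1.28 SD. If the planned effect size of 0.5 is a standardised mean difference (an assumption), pure partitioning yields 1.15/0.5 = 2.3 to 1.28/0.5 = 2.6 times that effect.

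**Does another part of the plan prevent this?** The random split of the dataset is placed under the mechanistic work and tied to factor analyses. It would not cure the problem by itself, since people in the second half assigned to profiles by the same variables would still differ on them.

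**The case against.** The strongest reply is that the article never says which variables are compared. It collects many baseline measures that are neither implied profile inputs nor clinical outcomes, such as cognitive tests, the neuropathy score, actigraphy and C reactive protein. Tests on these, where unrelated to the profiling, keep about their nominal level. The wording is exploratory, and nowhere are these p-values said to establish that profiles exist. PCA alone gives scores, not groups. The article is condensed, and a fuller analysis plan may name the variables. All of this stands, and it is why the point is conditional. It does not remove it: the article names both the grouping methods and the tests, sets outcomes apart, and excludes nothing.

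A reader might also infer more than the documents support:

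- **That the stated belief is confirmed by construction.** The belief is differential: QST marks one kind of profile and CAP another. With correlated inputs nearly every input differs between clusters, which does not show that separation.
- **That the 12-week analysis is circular.** Pain at 12 weeks is a later outcome and not a baseline input, so that step does not share the defect.
- **That the tool is tested against profiles containing CAP.** Data analysis sets out no such test. Only the abstract's general phrase links profiling to tool evaluation.
- **That admitting CAP raises its false-difference rate from about 5% to 77%.** This assumes CAP unrelated to QST, whereas the article reports an association.
- **That CAP must be removed from the profiling.** The sponsor expects CAP to identify a profile, so its inclusion is a legitimate design choice if its consequences are respected.

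**Conclusion.** The point holds in conditional form. If the two-sample tests are run on the variables that formed the profiles, which is the most natural reading, their p-values carry no information on whether distinct profiles exist. Rejection is about 72% to 100% per variable at n = 250 with none present, against about 5% for variables outside and unrelated to the profiling. The exact rates rest on k-means, normal data and assumed numbers of inputs and profiles; the direction follows from grouping and testing on the same variables. Separately, the abstract and Data analysis differ on the inputs. That difference matters wherever the profiles serve as a yardstick for the tool.

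**What to change.** 1. State one list of profile inputs and use it in both the abstract and Data analysis.
2. Report the forming variables by profile descriptively (means, spread, plots) without p-values.
3. Restrict between-profile tests to variables not used to form the profiles, and name them.
4. Allow a one-profile solution before calling patterns distinct, for example by BIC or a bootstrap likelihood-ratio test of one versus two classes.
5. If CAP or clinical QST stays among the inputs, say that those profiles will not serve as an external yardstick for the tool.

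The cost is wording in the analysis plan; no new data are needed. The downside is that fewer p-values are reported and that a finding of no distinct profiles becomes possible.

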### Participants

Inclusion (must meet all criteria):

Aged 18 years or older.One or more of the following physician confirmed or self-reported diagnoses: fibromyalgia, osteoarthritis, chronic low back pain, inflammatory musculoskeletal conditions (eg, rheumatoid arthritis (RA), psoriatic arthritis (PsA), axial spondylarthritis).Musculoskeletal diagnosis and pain onset ≥3 months.Self-reported pain ≥3/10, where 0 is ‘no pain’ and 10 is the ‘worst pain imaginable’ for most days in the 3 months before baseline.

Exclusion (if any of the following apply):

Unable to give informed consent.Terminal or uncontrolled medical or mental health condition precluding them from completing the study protocol or pose a significant risk to themselves or staff.Unable to comprehend spoken to written English, due to not all questionnaires being translated and validated in other languages, and due to the nature of QST, individuals need to fully comprehend the testing procedure to ensure reported outcomes are valid.

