### Outcomes

Primary outcomes:

The risk for persistent pain or pain worsening to a clinically important extent, using the risk stratification tool (combined clinical QST and CAP).Sensitivity and specificity of the risk stratification tool to identify people at risk of persistent and/or worsening pain.

Secondary outcomes:

External validity of the risk stratification tool against laboratory QST and validated questionnaires addressing central sensitisation-related characteristics.Internal validity of the risk stratification tool.Pain prognosis: Prediction of pain at 12 weeks by the risk stratification tool, CAP and clinical QST separately.Mechanistic underpinning: Investigate, according to the assessments outlined, which pain mechanisms contribute to risk levels identified using the risk stratification tool.Acceptability and feasibility of the risk stratification tool by patients, healthcare professionals (HCPs) and researchers within both research and clinical environments.Refinement of the risk stratification tool by patients, HCPs and researchers.Inter-rater and intrarater reliability of the risk stratification tool.

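### The prognosis analysis screens its comparators and chooses the CAP/QST combination in the same roughly 200 completers, so added value and accuracy are likely to be overstated unless corrected

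*Protocol article*

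**What the plan says.** The Outcomes section lists two primary outcomes. One is the risk of persistent or worsening pain, assessed "using the risk stratification tool (combined clinical QST and CAP"; the other is "Sensitivity and specificity of the risk stratification tool to identify people at risk of persistent and/or worsening pain". Pain prognosis is a secondary outcome: "Prediction of pain at 12 weeks by the risk stratification tool, CAP and clinical QST separately".

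The pain prognosis item of the Data analysis section has three steps:

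- **Screen.** "Bivariable correlations will identify and permit comparison between baseline factors significantly associated with 3-month pain prognosis".
- **Benchmark.** Separate multivariable models test whether CAP, clinical QST or laboratory QST improves on the other clinical and demographic variables that are significantly related to prognosis.
- **Choice of combination.** Multivariable modelling then settles whether CAP and QST give an important gain and in which mix. The share of prognosis explained is reported.

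The 12-week outcome is given by examples (persistent or worsening pain, or pain above the patient acceptable symptom state) and is described as "informed by patterns of pain over 12 weeks and knowledge".

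On validation, the article says "The dataset will be randomly divided into development and validation sets". That sentence opens the mechanistic underpinning item and is followed by exploratory and confirmatory factor analyses.

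On numbers: "A sample size of 250 participants at baseline, with an anticipated 200 individuals completing the follow-up questionnaires, accounting for 20% attrition".

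**The concern.** Two selection steps use the outcome data on which the result is then judged.

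First, a significance screen at n = 200 misses many modest but real predictors. If a missed predictor is correlated with CAP or QST, its effect is credited to CAP or QST. The analysis may then report prognostic gain that a properly adjusted model would not show.

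Second, when the combination, its weights and possibly a cut-off are chosen in the same people in whom performance is measured, R², sensitivity and specificity are biased upward. The split that could guard against this is not attached to the prognosis models or to sensitivity and specificity.

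What is at stake is whether the combined tool beats CAP or QST alone, and how accurate it will look to the clinicians for whom it is intended.

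**Working it through.** **Analysis set.** 250 × (1 − 0.20) = 200. The plan's figure reproduces.

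**1. How often the screen keeps a real predictor.** Assumptions: two-sided p < 0.05 and true r = 0.15. The Sample size section quotes 0.15 as a correlation with 12-week pain.

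- Smallest significant correlation at n = 200: 1.972 / √(198 + 1.972²) = 0.139.
- Fisher z: atanh(0.15) × √(200 − 3) = 0.1511 × 14.04 = 2.12.
- Probability of being kept: Φ(2.12 − 1.96) = Φ(0.16) ≈ 0.56.
- With five such predictors, 5 × 0.44 = 2.2 are lost on average.

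The Sample size section pairs 0.15 with 164 participants and 95% power. Read as a simple correlation, that pairing would need 572 (two-sided). That is a separate matter, and nothing here depends on 164.

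**2. What this does to the claim that CAP adds value.** Simulation, n = 200: five real predictors, each with r = 0.15 with the outcome, and a CAP score correlated with them but with no effect of its own. The test of CAP's added contribution was falsely positive in 17% of studies after screening, against 5% with all five fixed in the model. The size depends on the assumed correlation between CAP and each predictor. A check with mutually independent predictors gave:

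| Correlation of CAP with each predictor | Screened | Fixed |
|---|---|---|
| 0.2 | 9% | 4% |
| 0.3 | 16% | 5% |
| 0.4 | 34% | 5% |

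**3. Choosing and judging the tool in the same people.** Simulation using the tool's components from the Abstract (CAP, PPT, TSP, CPM, tender point count). Assumptions: n = 200, pairwise correlation 0.2, a fitted linear score and a cut-off at the maximum Youden index (sensitivity + specificity − 1).

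| Cases | Apparent, no true effect, all five | Apparent, no true effect, best combination | Apparent, modest effects, best combination | New data, modest effects |
|---|---|---|---|---|
| 50% | 0.18 | 0.21 | 0.29 | 0.14 |
| 70% | 0.20 | 0.23 | 0.31 | 0.13 |
| 85% | 0.26 | 0.29 | 0.35 | 0.11 |

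Modest effects are standardised differences of 0.4, 0.2, 0.2, 0 and 0. A separate five-component calculation gave 0.27 to 0.32 apparent against 0.12 to 0.14 in new data. Choosing the combination adds only about 0.03 (for example 0.21 − 0.18). Most of the optimism comes from fitting the weights and cut-off in the same data.

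**4. Does the proposed correction work?** With four predictors fixed in advance, 50% cases and a data-chosen cut-off, apparent Youden was 0.30 to 0.34, new-data 0.20 to 0.25, and bootstrap-corrected 0.22 to 0.27. With predictors screened from 20 candidates and the screen repeated in each resample, the figures were 0.29 to 0.37, 0.13 to 0.23 and 0.15 to 0.25. The corrected value lay within about 0.03 of the truth in each case.

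**The case against.** **Stronger readings the documents do not support.** A reader might infer that the tool's own predictors are picked by bivariable significance. They are not: the components (clinical QST and CAP) are named in advance, and the screen supplies the comparator variables for a secondary outcome. A reader might also take "informed by patterns of pain over 12 weeks and knowledge" to mean that the outcome will be chosen after seeing which one the tool predicts. The phrase closes the pain-profiling item and is ambiguous; it may only mean that the weekly pain reports guide interpretation. Finally, since entrants already had pain "for most days in the 3 months before baseline", a reader might infer too few non-cases to estimate specificity. That is a separate question of precision, and it needs an event rate that the article does not give.

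**The screen may do no harm.** With 30 null comparators and four null tool variables, the mean gain in R² was 0.020 with screening and 0.020 with five fixed covariates. False-positive rates were 5.5 to 5.7% and 5.3 to 5.5%. This stands for chance-selected comparators. It does not cover the loss of real predictors correlated with CAP, which is the mechanism in step 2. Such correlation is plausible: CAP items cover fatigue, mood, sleep and cognition, which the study also measures separately.

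**Cut-off and internal validation are details for a full protocol or SAP.** This largely stands. The article states no cut-off rule, and optimism correction may be specified elsewhere. The conclusion is therefore conditional. The screen, the data-driven choice of combination and the placement of the split are nevertheless stated choices.

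**Conclusion.** The point holds as a should-fix improvement to a stated method. Comparators are chosen by significance against the same 12-week outcome, the CAP/QST combination is chosen in the same roughly 200 completers, and the article's only development/validation split is tied to the factor analyses.

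Two consequences follow. The added value of CAP or QST can be credited falsely: 17% against 5% in the illustration, and 9% to 34% as the assumed correlation runs from 0.2 to 0.4. Apparent R², and sensitivity and specificity (one of two primary outcomes), are likely to be overstated unless corrected. With a data-chosen cut-off the Youden index is inflated by roughly 0.15 or more under the modest-effect assumptions. If the score and cut-off are fixed beforehand, most of that second effect disappears.

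The number of real predictors, their correlation with CAP, the case proportion and the cut-off rule are all assumed. The direction is well supported; the sizes are illustrative. The documents do not show that performance will be overstated, because a correction may be specified in a plan that is not shown.

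**What to change.** - **Covariates.** Replace the significance screen with a set fixed in advance: baseline pain, age, sex and diagnosis indicators. Add CAP, clinical QST and both in turn, and report the gain at each step.
- **Optimism correction.** Report bootstrap-corrected R², AUC, sensitivity and specificity on all completers. Repeat every selection step (the combination and any cut-off) in each resample.
- **Outcome.** Choose the single 12-week definition for sensitivity and specificity from the options already named, before 12-week data are examined. Say what the weekly pain patterns are meant to inform.

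The cost is wording in the analysis plan and more computation. Reported performance will be slightly less favourable. No additional participants or measurements are needed. Recruitment is still under way, with the study expected to end in April 2027, so the changes can be dated before the prognosis analysis.
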